**3 . MATERIAL AND METHODS**

**3.1 Experimental design:** the research is designed as a *crossover clinical trial* .

3.2 Description and selection of the population and sample: 22 subjects with type 2 diabetes treated at the Health Centers of Núcleo Bandeirante, Riacho Fundo I or Candangolândia will participate in this study. They will be invited to participate by putting up posters and giving lectures to publicize the study that will take place at the UPA of Núcleo Bandeirante. The sample size was defined considering the results of the study of De Carvalho *et al.* (‎2017) and the calculation was made by the *G Power* program version 3.1.9.2 (University of Düsseldorf, Germany), which indicated the need for at least 19 participants in each experimental group, to which we added 15% to compensate for possible losses. A significance level of 5% was adopted.

The inclusion criteria will be: to have a diagnosis of type 2 diabetes (American Diabetes Association , 2017); age between 30 ≥ and < 60 years; to consume breakfast regularly (≥ 100 kcal ingested, within 2 hours after waking up, on ≥ 4 days of the week); to be not allergic to the foods tested/used in the study; to agree to eat all study foods; to report no sleep disorders or use sleeping medication; to have availability of time to participate in all meetings within a period of up to 3 months and to agree to participate in the research by signing the Free and Informed Consent Form (TCLE).

Subjects that will be excluded from the study are those who: use exogenous insulin or medications for pathologies other than DM2; have complications from diabetes; smoke; have gastrointestinal disorders or irregular intestinal rhythm; have psychiatric disorders with impaired understanding; participate in other research protocols; refuse to provide or are not able to provide relevant data to the research and who do not attend previously scheduled tests for three times after confirming their presence in the day before the intervention.

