**3.5 Statistical Analysis:**

Sample characterization data and meal palatability will be analyzed using the mean ± standard deviation. To compare the average palatability scores, the Shapiro- Wilk test will be applied.

To examine the effects of the tested meals and time on blood glucose, two-way analysis of variance (ANOVA) with repeated measures will be performed with *post hoc* comparisons using the Bonferroni adjustment.

The areas under the glycemic curve (AUC) will be calculated using the trapezoidal method, considering the area above baseline values (Tosh, 2013). The Shapiro-Wilk, Levene and Mauchly tests will be applied to assess whether the data present normal distribution, homoscedasticity and sphericity, respectively. The effect of the tested meals on glycemic AUC or appetite scores will be measured by one-way ANOVA with repeated measures with Bonferroni *post hoc comparisons* .

The tests will be carried out using the SPSS Statistics software version 21.0 (IBM Corporation) with a significance level of 5% being accepted.

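### The planned repeated-measures ANOVA drops any participant with a gap while the loss allowance covers only three, and two of its assumption checks do not fit the whole design

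*Protocol*

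**What the plan says.** Protocol section 3.5 fixes the methods and the software:

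- Curves: for meal and time effects on glucose, "two-way analysis of variance (ANOVA) with repeated measures will be performed", followed by Bonferroni post hoc comparisons.
- AUC: "The effect of the tested meals on glycemic AUC or appetite scores will be measured by one-way ANOVA with repeated measures", also with Bonferroni.
- Assumption checks: "The Shapiro-Wilk, Levene and Mauchly tests will be applied to assess whether the data present normal distribution, homoscedasticity and sphericity, respectively". This sentence stands in the AUC paragraph, directly before the one-way ANOVA. The paragraph on the two-way ANOVA names no sphericity test.
- Software: "The tests will be carried out using the SPSS Statistics software version 21.0 (IBM Corporation) with a significance level of 5% being accepted".

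Sections 2.2 and 3.4 give 13 meals (the standard breakfast alone and with each of 12 additions) and seven glucose readings per meal. Section 3.2 gives 22 participants: at least 19, plus 15% for losses. It also excludes subjects "who do not attend previously scheduled tests for three times after confirming their presence" the day before. Section 3.4 moves a visit to another date when home glucose is out of range. The protocol does not say how gaps in the data are handled.

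**The concern.** Classical repeated-measures ANOVA treats each participant as one row that must be complete. With 13 visits each, a single absence removes the other 12 sessions from the AUC analysis. In the two-way model, one failed reading out of 91 does the same. The 15% allowance is sized for people who leave the study, whereas the analysis loses a person for any gap.

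Gaps are plausible. Section 3.2 asks for all visits within 3 months, and section 3.4 sets a washout of 3 to 10 days. Twelve washouts span 36 to 120 days, and a 90-day window allows a mean gap of 90/12 = 7.5 days, which limits how often a visit can be moved.

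The second issue is the assumption checks. Objectives III and IV in section 2.2 compare the curves time by time and in shape, which is the meal-by-time interaction. If Mauchly's test is meant to cover that interaction, it cannot be run. The choice between an uncorrected and a corrected test would then be open once the data are in, and that choice changes the error rate considerably.

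**Working it through.** **1. The plan's own figure.** 19 × 1.15 = 21.85, rounded up to 22, which matches section 3.2. The base figure of 19 cannot be rebuilt, because the section gives no effect size, SD, correlation or power. The allowance is 22 − 19 = 3 incomplete participants.

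**2. Smallest number of gaps that breaches 19.** There are 22 × 13 = 286 sessions and 22 × 13 × 7 = 2,002 readings. Four missed sessions in four different people (4/286 = 1.4%) leave 18. In the two-way model, four failed readings in four people (4/2,002 = 0.2%) also leave 18.

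**3. Expected complete participants.** The loss rates are assumptions, taken as independent between sessions or readings. Formulas: 22 × (1 − m)^13 for sessions and 22 × (1 − m)^91 for readings.

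| Unit lost | Rate m | Share complete | Complete of 22 |
|---|---|---|---|
| Session | 1% | 0.878 | 19.3 |
| Session | 2% | 0.769 | 16.9 |
| Session | 5% | 0.513 | 11.3 |
| Reading | 0.1% | 0.913 | 20.1 |
| Reading | 0.2% | 0.833 | 18.3 |
| Reading | 0.5% | 0.634 | 13.9 |

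To expect 19 complete, session loss may be at most 1 − (19/22)^(1/13) = 1.1%, and reading loss at most 1 − (19/22)^(1/91) = 0.16%.

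**4. Effect on power.** For one paired comparison (two-sided 5%, 80% power, before any Bonferroni adjustment), the detectable standardised difference is 0.63 with 22 participants, 0.68 with 19, 0.78 with 15 and 0.94 with 11.

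**5. Where Mauchly's test exists.** The test needs a contrast covariance matrix of full rank, and the rank cannot exceed n − 1 = 21.

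- Meal effect and AUC: 13 − 1 = 12 contrasts, computable. It fails only with 12 or fewer complete participants.
- Time effect: 7 − 1 = 6 contrasts, computable.
- Meal by time: 12 × 6 = 72 contrasts. The rank is 21, the determinant is zero, and there is no test.

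**6. What the open choice does to the interaction test.** This was simulated with no true effect, 22 complete participants, 3,000 runs per scenario, equal covariance for every meal, and assumed correlations between readings 15 minutes apart. Ranges cover equal and time-varying variances. Nominal level 5%.

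| Correlation at 15 min | Uncorrected | Greenhouse-Geisser | Huynh-Feldt |
|---|---|---|---|
| 0 | 4.1% to 6.0% | 0.0% | 3.8% to 5.2% |
| 0.5 | 6.2% to 8.1% | 0.2% to 0.3% | 4.9% to 5.4% |
| 0.8 | 9.7% to 9.9% | 0.2% to 0.3% | 4.9% to 5.1% |
| 0.95 | 12.6% to 12.7% | 0.7% to 1.0% | 5.0% to 5.1% |

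Greenhouse-Geisser is very conservative here because its estimate cannot exceed 21/72 = 0.29, even when sphericity holds.

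**7. Does a mixed model settle sphericity?** Not by itself. With complete balanced data and positive variance components, a model with random participant, participant × meal and participant × time and independent errors gives the same F test as the uncorrected column above. For AUC, a random-participant model imposes compound symmetry and reproduces the uncorrected one-way F test. A fully unstructured covariance over 91 cells has 91 × 92/2 = 4,186 parameters against 2,002 readings, so it cannot be fitted.

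**8. Levene's test.** It compares variances between independent groups. All 13 conditions are measured in the same people, so there are none.

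**The case against.** The case against has several sound parts.

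- **Missing-data handling often sits in a SAP.** The protocol never states listwise deletion, and a SAP not shown here could address gaps. That stands as a limit on certainty. But the protocol does fix classical ANOVA in SPSS, and dropping incomplete participants follows from that method as normally run. The point is the method chosen, not a missing detail.
- **The loss rates are assumed.** They are. Absences tend to cluster: 2% of 286 sessions is about six, which could fall on one person or on six. Out-of-range days are rescheduled, not lost. Both lower the number of incomplete participants, so the independent-loss figures lean towards the worst case. The count of four people with one gap each needs no rate.
- **The Mauchly sentence belongs to the AUC paragraph**, where the test works. This stands. A reader might infer that the plan makes the interaction test depend on Mauchly, but no such rule is written; the text is at most ambiguous.
- **An untestable assumption does not make the ANOVA unusable.** This also stands. Epsilon corrections need no pretest, and Huynh-Feldt held close to 5% in the simulated scenarios.

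Three further inferences are tempting and unsupported. Section 3.2 does not say that the completed sessions of participants excluded for repeated absence are deleted, and its rule counts only absences after confirmation the day before. Nothing shows that complete participants will be the better-controlled ones; they may be, if rescheduling runs out of time. And a mixed model does not cure both problems for free, as step 7 shows.

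**Conclusion.** The point holds in a limited form and is moderate in severity. The planned ANOVA, as normally run in SPSS, tolerates three incomplete participants before falling below the plan's own minimum of 19. Four people with one missed session each are enough to breach it. Under assumed independent session loss of 1%, 2% or 5%, about 19, 17 or 11 of 22 remain, and fewer are lost with clustering or successful rescheduling. That rests on the method and software named in section 3.5, not on an explicit deletion rule.

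On the assumption checks, Levene's test does not apply to this design. Mauchly's test is usable for AUC, meal and time with 22 or 19 complete participants, but not for the interaction. The sphericity gap is therefore confined to the interaction and can be closed by an epsilon correction or a suitable covariance structure. The documents do not support the stronger reading that the analysis is invalid as planned.

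**What to change.** Amend section 3.5 before any data are examined:

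1. **AUC.** Use a linear mixed model with fixed meal, random participant and Satterthwaite degrees of freedom, on every completed session. As a sensitivity analysis, let variances differ by meal or report an epsilon-corrected ANOVA, because the main model assumes compound symmetry.
2. **Curves.** Prespecify one of two routes.
   - A mixed model with fixed meal, time and meal × time; random participant, participant × time and session; a named within-session covariance; and small-sample degrees of freedom. The covariance must suit the unequal 15- and 30-minute gaps; plain AR(1), which treats all steps as equal, does not. Confirm that the chosen structure is available in the SPSS version named.
   - Or keep the ANOVA and apply a Huynh-Feldt correction to the interaction without a pretest. This leaves the loss of incomplete participants in place for the curves.
3. **Checks.** Delete Levene's test and state that Mauchly's test is not relied on for the interaction.
4. **Completed sessions.** State that sessions already completed by participants who stop attending stay in the analysis.

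The cost is analysis wording, with no new data. There are two downsides: a covariance structure must be named in advance, and keeping partial data is valid only under missing at random.

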**3.4 Intervention**

The intervention will take place from 05/01 to 08/30/2019.

Participants will measure their capillary blood glucose before leaving home and, if their blood glucose level is lower than 80 mg/dL or higher than 200 mg/dL, they will not participate in the intervention on that day, and another date will be scheduled. Subjects must arrive at the place where the intervention will take place (at the UPA of Núcleo Bandeirante) between 7:00 am and 8:30 am, and fasting for 8 to 11 hours. In the night before, everyone will eat two standard meals (dinner and supper).

In random order, they will be instructed to consume the standard breakfast, or a standard breakfast plus one of the test foods (foods that will be tested: 3 g of cinnamon powder; 3 g of cinnamon in capsules; 6 g of cinnamon powder; 6 g of cinnamon in capsules; 100 g of lettuce; 100 g of tomato; 30 ml of extra virgin olive oil; 115 g of mixed salad containing 50 g of lettuce, 50 g of tomato and 15 ml of extra virgin olive oil; 150 g of avocado; 15 g of wheat bran; 15 g of chia seeds or 15 g of golden flaxseed flour), within 15 minutes. After consuming each meal, participants will complete the Visual Analogue Scale (**ANNEX II**) to assess palatability, considering appearance, smell, texture, flavor and intensity of flavors (sweet, salty, bitter and sour) (Flint *et al.* , 2000). The glycemic curve will be monitored for 120 minutes at times 0, 15, 30, 45, 60, 90 and 120 minutes. Capillary blood glucose determination will be carried out using the Accu-Check Active device (Roche Diagnostics) made available by the researcher and will be the option of choice so that glycemic results are known quickly and the patient is not exposed to the risk of unmonitored hypoglycemia. The positive area formed below the glycemic response curve will be calculated using the trapezoidal method. Washout application will be for a minimum of 3 days and a maximum of 10 days.

Table 1 presents the nutritional information of the standard breakfast that will be offered to patients. The nutritional value corresponds to approximately 15% of the total energy value of a standard diet of 2,000 kcal, containing 59.4% carbohydrates, 28.6% lipids and 12.0% proteins and is in accordance with the Brazilian Diabetes Society Guidelines (2017).

Table 1. Nutritional information for the standard breakfast

| **Food** | **Quantity** | **CHO (g)** | **LIP (g)** | **PTN (g)** | **Fibers (g)** | **Lime** |

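### Cheap improvement: the time-0 reading carries most of the meter error in the area above baseline, so duplicating it would sharpen that AUC

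*Protocol*

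**What the plan says.** Section 3.4 of the protocol sets the sampling scheme: "The glycemic curve will be monitored for 120 minutes at times 0, 15, 30, 45, 60, 90 and 120 minutes". The instrument is a capillary meter: "Capillary blood glucose determination will be carried out using the Accu-Check Active device". No duplicate or averaged fasting value is described. The word single is not used either, so one reading per time is the natural inference rather than an explicit statement.

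The only other pre-meal measurement is the check at home, which postpones the session "if their blood glucose level is lower than 80 mg/dL or higher than 200 mg/dL". It decides attendance and is not named as a baseline for the curve.

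Section 3.5 defines the AUC by the trapezoidal method, "considering the area above baseline values". Section 3.4 describes the same outcome as a positive area: "The positive area formed below the glycemic response curve will be calculated using the trapezoidal method". Section 3.5 then carries it into the comparison of meals: "The effect of the tested meals on glycemic AUC or appetite scores will be measured by one-way ANOVA with repeated measures", with Bonferroni comparisons. Specific objective IV in section 2.2 names this area as something to be analysed. The protocol gives no precision figure for the meter and no within-patient SD for the AUC.

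**The concern.** In an area above baseline, the baseline value is subtracted from the curve over the whole observation period. Error in that one reading is therefore multiplied by nearly the full 120 minutes, while error in any later reading is multiplied only by its own trapezoid width. For example, an assumed meter error of 7 mg/dL at time 0 moves the AUC by 7 x 112.5 = 787.5 mg.min/dL. That equals a shift of the whole curve by 787.5/120 = 6.6 mg/dL for two hours.

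Baseline meter errors on different days are separate errors, so they do not cancel when a patient's meals are compared. They enter each contrast of a test food with the standard breakfast as noise. The scheme spends the same measuring effort at each time, although the chosen outcome is far more sensitive to one of them. A later SAP cannot recover a reading that was never taken, so the place to act is section 3.4.

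**Working it through.** The protocol states no figure on this point, so there is none to reproduce.

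**Inputs.** The sampling times (section 3.4) and the area above baseline (section 3.5) come from the protocol. Error sizes, post-meal glucose levels and error correlations are assumptions and are marked as such.

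**Weights.** For times 0/15/30/45/60/90/120 the trapezoid weights are 7.5, 15, 15, 15, 22.5, 30 and 15 minutes (sum 120). The area above baseline is the sum of w_i(G_i - G_0), so the coefficient on G_0 is 7.5 - 120 = -112.5. The other coefficients stay at 15, 15, 15, 22.5, 30 and 15. In absolute size, time 0 has 112.5/30 = 3.75 times the weight of the next heaviest reading (90 min).

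**Equal, independent errors at every reading (assumed).**
- Time 0: 112.5^2 = 12,656.25.
- The other six: 3 x 225 + 506.25 + 900 + 225 = 2,306.25.
- Share of time 0: 12,656.25/14,962.5 = 84.6%.
- With two time-0 readings averaged: 6,328.1 + 2,306.25 = 8,634.4, a cut of 42.3%.
- For an assumed meter SD of 5, 7 or 10 mg/dL, the meter-error SD of the AUC falls from 612, 856 or 1,223 to 465, 650 or 929 mg.min/dL.

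**Error proportional to glucose (assumed).** If post-meal values are on average r times baseline, the share is 12,656.25/(12,656.25 + 2,306.25 r^2), and the cut is half of that.

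| r (assumed) | Time-0 share | Cut from a duplicate |
|---|---|---|
| 1.16 | 80.3% | 40.2% |
| 1.46 | 72.0% | 36.0% |
| 1.8 | 62.9% | 31.4% |
| 2.0 | 57.8% | 28.9% |

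An assumed curve of 130-150-180-205-210-190-165 mg/dL gives 72.1% and 36.1%.

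**Positive-area rule.** The linear weights hold while glucose stays above baseline. A simulation that counts only positive area (assumed baseline 100-180 mg/dL, rise 20-80 mg/dL, CV 3-7.5%) gives shares of about 67-85% and cuts of about 34-42%. The rule changes little.

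**Duplicates elsewhere, same sampling times.** With equal errors, duplicating the 90-minute reading cuts (900/2)/14,962.5 = 3.0%, and duplicating all six later readings cuts (2,306.25/2)/14,962.5 = 7.7%. In the proportional case with r = 2, all six together cut (100 - 57.8)/2 = 21.1%, still below the 28.9% from time 0 alone.

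**Correlated duplicates.** If the two time-0 errors have correlation rho, the cut is share x (1 - rho)/2. With the 84.6% share, an assumed rho of 0.3, 0.5 or 0.7 gives 30%, 21% or 13%.

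**Total variance.** If meter error is a fraction f of within-patient AUC variance, the total falls by f times the meter-error cut. For an assumed f of 10-50% and independent duplicates, that is 4-21% at the 42.3% cut and 3-14% at the 28.9% cut. The protocol does not supply f.

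**Contrast.** For a total AUC without baseline subtraction, time 0 would carry only 56.25/2,362.5 = 2.4% of the error variance. The sensitivity comes from the baseline-subtracted outcome.

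**The case against.** The strongest reply is that nothing here is wrong. The two sections fit together, the area above baseline is a workable outcome, and random meter error adds noise without favouring any food. That stands, and it makes this an improvement and not a defect.

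Several narrower points also stand:
- The repeated-measures ANOVA works with total within-patient variation, which includes day-to-day biology that a second strip does not touch. A reader might infer that the AUC comparison gains 29-42% in precision or power; the protocol gives no figures to support that.
- The shares under proportional error depend on a post-meal rise that the protocol does not give. A reader might infer that the AUC's error comes almost entirely from time 0. At 58-85%, mostly is the accurate word.
- Halving the time-0 error variance requires independent errors. Two strips from one puncture can share contamination or local sample effects that averaging leaves in place.
- A reader might infer that a second time-0 reading beats any other use of a strip. The check covers only duplicates at the existing times. New times inside the two 30-minute gaps would address interpolation error, which was not examined.
- The meal-by-time ANOVA compares glucose at each time, where time 0 has no special weight, so it is largely unaffected.

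The objection does not remove the main point. Time 0 was the largest source of the AUC's meter error in every case tried, and the remedy is inexpensive.

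**Conclusion.** The point holds as a cheap improvement in precision. With the protocol's sampling times and its area above baseline, the time-0 reading carries 85% of the AUC's meter-error variance if errors have equal SD. It carries about 58-80% if error is proportional to glucose and post-meal values average roughly 1.16 to 2 times baseline. A duplicate with independent error cuts meter-error variance by about 29-42%; correlated errors reduce this, for example from 42% to 21% at a correlation of 0.5. The effect on total within-patient variance, and so on power, is smaller and cannot be derived from the protocol. All of this assumes one reading per time, as section 3.4 implies, and errors that are independent between times.

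The documents do not support reading this as a flaw that biases the comparison of foods or invalidates the AUC analysis.

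**What to change.** In section 3.4, state that two time-0 readings are taken on the study meter at each session, from separately collected drops where acceptable, so that their errors are closer to independent. In section 3.5, state that their mean is the baseline for the area above baseline. Keep single readings at the other six times. For the meal-by-time ANOVA, say whether the first reading or the mean is used; the first reading keeps the same measurement precision at all seven times. If duplicates were already intended, section 3.4 only needs to say so.

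The cost is up to 13 meals x 22 participants = 286 extra strips, and possibly a second finger puncture per session. No visit is added, and no meal, attendance rule or other management rule changes.

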**2.2 Specifics:**

**I)** To measure the glycemic response at times 0/15/30/45/60/90/120 minutes after consumption of the tested meals, which will be:

- Standard breakfast;

- Standard breakfast plus 3 g of cinnamon powder;

- Standard breakfast plus 3 g of cinnamon capsules;

- Standard breakfast plus 6 g of cinnamon powder;

- Standard breakfast plus 6 g of cinnamon capsules;

- Standard breakfast plus 100 g of lettuce;

- Standard breakfast plus 100 g of tomato;

- Standard breakfast plus 30 ml of extra virgin olive oil;

- Standard breakfast plus 115g of mixed salad containing 50 g of lettuce, 50 g of tomato and 15 ml of extra virgin olive oil;

- Standard breakfast plus 150 g of avocado;

- Standard breakfast plus 15 g of wheat bran;

- Standard breakfast plus 15 g of chia seeds and

- Standard breakfast plus 15 g of golden linseed flour;

**II)** – To check the effect of the tested meals on palatability;

**III)** To compare the time-to-time glycemic responses resulting from the evaluated meals and

**IV)** – To analyze the behavior of the curve and the area below the glycemic curve (at times 0/15/30/45/60/90/120 minutes) after consuming tested meals.

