**Questionnaire to evaluate palatability**

Volunteer name:

___________________________ Nº randomização: _________ Fase:

Date: ________________

Time: ________

Favor marcar na escala o que melhor reflete a sua resposta para cada uma das questões abaixo:

Não estou faminto

Nunca estive

em absoluto

tão faminto

Não estou cheio

em absoluto

Totalmente cheio

Completamente

Não poderia

vazio

comer

mais

nada

Muito mais

Nada mais

Nada

Extremadamente

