**After eating all the food in the meal, evaluate it, considering the parameters presented below:**

Weak

Strong

Sourness

Saltiness

Strong

Weak

Saltiness

Strong

Sweetness

Weak

Strong

Weak

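### Appetite scores are tested with no appetite objective and no planned pre-meal score; under random meal order this costs precision and does not bias the meal comparison

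*Protocol*

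**What the plan says.** - **Analysis (protocol, 3.5).** "The effect of the tested meals on glycemic AUC or appetite scores will be measured by one-way ANOVA with repeated measures". Pairwise tests follow, adjusted by the Bonferroni method. Appetite thus gets the same formal test as glycemic AUC.
- **Objectives (protocol, 2.2).** Objectives I, III and IV concern glucose. Objective II is "To check the effect of the tested meals on palatability". None names appetite, hunger or satiety.
- **Collection (protocol, 3.4).** "After consuming each meal, participants will complete the Visual Analogue Scale"; the stated purpose is "to assess palatability, considering appearance, smell, texture, flavor and intensity of flavors". Hunger and fullness are not listed, and no pre-meal or later time is given.
- **Form (protocol, Annex II).** Hunger and fullness lines appear in Portuguese, for example "Não estou faminto" (I am not hungry), following the title "Questionnaire to evaluate palatability". The form has blank fields for date, time and phase. The instruction "After eating all the food in the meal, evaluate it, considering the parameters presented below" stands with the taste items.
- **Design (protocol, 3.4).** "In random order, they will be instructed to consume the standard breakfast", or that breakfast plus one test food. Two standard meals are eaten the evening before, the fast is 8 to 11 hours, and arrival is between 7:00 and 8:30 am.

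**The concern.** Appetite is set up as a tested outcome, but the protocol does not say what question the test answers or when the score is taken. The only timing that could apply to the hunger and fullness lines is after the meal.

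A post-meal score depends partly on how hungry the participant was on arrival. The permitted fasting and arrival windows allow that to differ between sessions of the same person. For glucose the plan deals with the starting level, because AUC is taken above baseline. For appetite it has no counterpart, either in collection or in analysis.

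Two things are at stake. An appetite result would answer no stated objective. It would also be less precise than it need be, so a null result would say little. A pre-meal score that was not collected cannot be recovered by any later analysis plan, which makes this a matter for the protocol.

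**Working it through.** **1. What the appetite endpoint can be.** Setting sections 2.2, 3.4, 3.5 and Annex II side by side:

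| Feature | Glucose | Appetite |
|---|---|---|
| Objective in 2.2 | I, III, IV | none |
| Times in 3.4 | 0, 15, 30, 45, 60, 90, 120 min | none of its own; the annex is completed after the meal |
| Starting level of the session | AUC taken above baseline | no pre-meal score stated |
| Analysis in 3.5 | two-way (meal, time) and one-way on AUC | one-way on the score |

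A one-way analysis has no time factor, and no appetite area or change score is defined. Followed literally, the test compares post-meal scores across 13 meals (the standard breakfast and 12 additions).

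**2. Sample size used below.** Section 3.2 gives 19 participants plus 15%: 19 × 1.15 = 21.85, rounded up to 22, which matches the stated 22. The 19 itself cannot be rebuilt, because effect size, SD and power are not given. The appetite point does not depend on it.

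**3. Bias or noise?** Write the post-meal score of participant i at meal j as

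Y_ij = participant_i + meal_j + hunger_ij + error_ij.

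With meals in random order within participant, hunger on arrival is unrelated in expectation to which meal is served. The term hunger_ij therefore joins the residual, whose variance becomes σ²_error + σ²_hunger.

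This was checked by simulating the planned one-way repeated-measures ANOVA: 22 participants, 13 meals, random order, 4,000 runs per setting. All variability values are assumptions on a 100-point scale: participant SD 15; residual SD 15; session-hunger SD 0, 10 or 20; drift of 0 or 1 point per visit. With no true meal effect, the rejection rate with hunger left in was 4.7% to 5.4% across the six settings, against a nominal 5%.

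**4. Loss of precision.** Let one meal of the 13 be shifted by 10 points. The noncentrality of the F test is

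λ = n × δ² × (1 − 1/k) / (σ²_error + σ²_hunger) = 22 × 100 × (12/13) / (225 + σ²_hunger) = 2,030.8 / (225 + σ²_hunger),

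with 12 and 21 × 12 = 252 degrees of freedom.

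| Hunger SD | Residual variance | λ | Power, noncentral F | Power, simulated (no drift) |
|---|---|---|---|---|
| 0 | 225 | 9.03 | 44% | 43% |
| 10 | 325 | 6.25 | 30% | 29% |
| 20 | 625 | 3.25 | 16% | 16% |

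With a drift of 1 point per visit the simulated powers were 42%, 29% and 16%.

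**5. What a pre-meal score could recover.** If the within-participant correlation of pre- and post-meal scores is ρ, adjustment multiplies the residual variance by 1 − ρ²:

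- ρ = 0.3: 1 − 0.09 = 0.91
- ρ = 0.5: 1 − 0.25 = 0.75
- ρ = 0.7: 1 − 0.49 = 0.51

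The first row of the table in step 4 is the limit in which hunger is removed completely. A pre-meal score that measures hunger imperfectly would recover only part of the gap.

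**6. Post hoc comparisons.** Thirteen meals give 13 × 12 / 2 = 78 pairs. If all are adjusted, each is tested at 0.05 / 78 = 0.00064, which leaves little precision to spare.

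**The case against.** **Randomisation already handles arrival hunger.** Meal order is random, the evening meals are standardised and the fast is bounded, so hunger balances in expectation and the F test allows for chance imbalance. This stands. A reader might infer that session-to-session hunger will be mistaken for a meal effect; the design does not support that, and the simulated error rate stays near 5%.

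**The protocol does not say the scale is given only once.** This also stands. Section 3.4 gives a post-meal time without excluding others, and the form has a blank time field. The order of lines in the text copy of Annex II is visibly disturbed, so the layout cannot show that the hunger lines are post-meal only. The point is limited to what is stated: the only time given is after the meal, and no pre-meal score is planned.

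**The appetite wording in 3.5 may be a loose or mistranslated reference to palatability.** The documents do not exclude this, and a pre-meal score would then be meaningless. But Annex II does carry hunger and fullness lines, so the wording has something to refer to. If the sponsor meant palatability, deletion under option (b) below settles it.

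**Baseline adjustment is for the analysis plan.** The choice of model is. Collecting the pre-meal score is not.

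A reader might also infer that a score taken straight after eating is too early for satiety differences between foods to appear. The protocol gives no basis for that, and it forms no part of this point.

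**Conclusion.** The point holds as an inconsistency with a precision cost. Section 3.5 tests an outcome that has no objective in 2.2 and no assessment time of its own in 3.4. As written, the test would rest on a post-meal score with no pre-meal score from the same session, and no change from pre-meal could be derived.

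The meal comparison is not biased. Session hunger stays in the error term. Under the assumed SDs, power for a 10-point shift in one meal falls from about 43% to 29% or 16%. Those figures illustrate the mechanism and are not estimates for this trial, because the protocol gives no variability for the scale; if arrival hunger varies little between sessions, the loss is small.

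The glucose time-point and AUC analyses are untouched, so the weight is minor.

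**What to change.** Choose one.

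**(a) Keep appetite.** Name it in 2.2 as a secondary or exploratory objective. Give the existing Annex II hunger and fullness lines immediately before as well as after each meal, and state both times in 3.4. In 3.5, analyse the post-meal score adjusted for that session's pre-meal score, in a linear mixed model with meal as a fixed effect and participant as a random effect. The mixed model is needed because the covariate changes from session to session. Cost: about one minute of form-filling per session, using scales already printed; no added participants or visits.

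**(b) Drop appetite.** Delete *or appetite scores* from 3.5 and the hunger and fullness lines from Annex II, and draw no appetite conclusion. If palatability was meant, say so in 3.5. Cost: a wording change.
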